### Objectives

The overall aim is to measure the effectiveness and cost effectiveness of "mini" and "full" booster sessions, as an adjunct to a brief intervention, in sustaining physical activity in middle-aged adults. The primary objective is to determine whether physical activity, measured by accelerometry three months after randomisation (six months after a brief intervention), is significantly increased in participants allocated to two intervention groups ("full" or "mini" booster) compared to participants allocated to a control group (receiving no further contact after the baseline assessment). Secondary objectives are as follows:

1. To determine whether physical activity nine months after randomisation (12 months after the brief intervention) is significantly increased in participants allocated to the two intervention groups compared to participants allocated to the control group.

2. To compare physiological measures of fitness (12 minute walk test) and self-reported physical activity (SPAQ) between allocated groups.

3. To compare health related quality of life, resource use (including health and social care contacts) and economic costs between allocated groups.

4. To investigate whether the impact of the intervention may be modified by gender, ethnicity or the types of physical activity undertaken (including use of community facilities for physical activity).

5. To undertake a process evaluation to identify, using both quantitative and qualitative methods, psychosocial and environmental factors that may mediate or modify the effectiveness of the intervention (this aspect of the study is the subject of a separate protocol and is not discussed further here).

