### Sample size

For the purposes of sample size estimation the primary outcome is an objective measure of physical activity and will be the mean physical activity levels from the 7-day accelerometric assessment (recoded as counts per week) at 3 months post-randomisation (6 months after initial contact). Kirk and colleagues suggest a standard deviation of approximately 1.2 million counts per week from a 7-day accelerometer assessment of 70 patients with type II diabetes [21]. We assume a mean difference of 400,000 counts per week between the intervention and control groups is the smallest difference of clinical and practical importance that is worth detecting. With 450 subjects (300 intervention: 150 control), the trial will have 90% power to detect this mean difference or greater between the "booster" arm and control arm (assuming a standard deviation of 1.2 million counts/week) as statistically significant at the 5% (two-sided) level using a two independent samples t-test.

With 300 subjects in the booster intervention (150 "mini": 150 "full" booster) the trial will have also have approximately 80% power to detect a similar mean difference of 400,000 counts per week between the two booster arms as statistically significant at the 5% (two-sided) level using a two independent samples t-test. Assuming an approximate 25-30% loss to follow-up by six-months, we proposed to recruit and randomise 200 subjects per group (600 in total). We will invite at least 30,000 40-64 year olds from the 20 most deprived neighbourhoods; we expect at least 1500 will receive the brief intervention of which we anticipate at least 40% will increase their physical activity and be eligible for randomisation. N = 600 divided equally between the three trial arms (200 per arm).

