### Statistical methods

The primary analysis will be of accelerometry data at three months post-randomisation. Analysis will be by intention-to-treat. A sensitivity analysis will be undertaken to impute missing accelerometry data using baseline and follow-up data from the group of participants with valid accelerometry data at three months post-randomisation. As this is an ITT analysis, withdrawals and protocol violations will be analysed in their groups as randomised.

All statistical exploratory tests will be two-tailed with alpha = 0.05. Baseline demographic variables (age, gender), physical measurements (e.g. weight, height, BMI), and health-related quality of life data (SF-36) will be summarised with appropriate summary statistics, tabulated and assessed for comparability between the treatment groups. For example, categorical variables, e.g. gender, the number and percentage of each category (e.g. male and female) will be reported. For continuous variables, e.g. age, reporting will depend on the distribution of the data, if it is symmetric, the data will be summarised with a mean and standard deviation; if it has a non-symmetric distribution it will be summarised with a median and inter-quartile range.

The primary aim is to compare the intervention ("full" or "mini" booster) versus control treatment (No booster), with a secondary aim of comparing the two interventions ("full" versus "mini" booster). The primary comparison will be between the mean physical activity levels from the accelerometer (counts per week) in the two "booster" arms combined compared with the mean physical activity levels in the control arm at 6 months follow-up (3 months post-randomisation). This difference in means, between the intervention and control groups, will be compared using a two independent samples t-test and a 95% confidence interval for estimated mean difference between the groups will also be calculated. In the event of differences between the booster and control groups with respect to baseline demographic, physical, and health-related quality of life measurements, multiple regression will be used to adjust the treatment effect for these variables. The ordinary least squares adjusted regression coefficient estimate for the treatment group parameter along with its 95% confidence interval (CI) will then be reported.

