Secondary outcomes such as HRQoL (SF-12v2 plus 4 dimension scores) and distance walked on 12 minute walk test, at three months post-randomisation, will be assumed to be continuous outcomes. A two independent samples t-test will be used to compare mean outcomes between the booster and control groups in this parameter. A 95% confidence interval (CI) for the mean difference in this parameter between the groups will also be calculated. In the event of differences between the booster and control groups with respect to baseline demographic, physical, and health-related quality of life measurements, multiple regression or analysis of covariance (ANCOVA) will be used to adjust the treatment effect for these variables. The ordinary least squares adjusted regression coefficient estimate for the treatment group parameter along with its 95% confidence interval (CI) will then be reported. Outcomes assessed at nine months post-randomisation will be analysed in a similar way. We shall also compare the effect of the two interventions ("full" versus "mini" booster) on these secondary outcomes at three and nine months post-randomisation, using the same methods as described above.

The health economic component of the study will estimate the incremental cost effectiveness of the "mini" booster and full booster interventions compared to no booster. It will include an estimation of the cost effectiveness of the intervention from a NHS perspective in terms of their incremental cost per quality adjusted life year (QALY) and a broader societal assessment of efficiency that includes costs for other Government agencies and productivity (inside and outside the home). It uses similar methods to those used in the successfully completed evaluation of a community exercise programme [22].

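### The nine-month accelerometry comparison leaves out the three-month readings of people lost in between, which costs some precision and can bias the result

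*Protocol article*

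**What the plan says.** The first secondary objective (Objectives) is "To determine whether physical activity nine months after randomisation (12 months after the brief intervention) is significantly increased" in the two intervention groups compared with control. Outcomes and Table 1 place seven-day accelerometry at three and nine months. The Discussion (Choice of outcome measure) explains why there is deliberately none at baseline.

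Statistical methods compares the combined booster arms with control at three months by a two-sample t-test. Regression adjustment is limited to baseline variables, and applies only if the groups differ on them. For the later visit the text is "Outcomes assessed at nine months post-randomisation will be analysed in a similar way". No joint or repeated-measures model is named, and the three-month reading is not a listed covariate.

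The one missing-data step is a sensitivity analysis to "impute missing accelerometry data using baseline and follow-up data from the group of participants with valid accelerometry data at three months post-randomisation". Sample size assumes 25-30% loss by six months after initial contact, which is three months after randomisation. It gives no figure for nine months.

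**The concern.** A two-sample t-test at nine months can use only people with a nine-month reading. Someone measured at three months and then lost contributes nothing, although the three-month reading is the only earlier objective information on that person's activity.

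Two things are at stake. The first is precision at the visit where cumulative loss is likely to be greatest. The second is possible selection. If less active people are more likely to miss the nine-month visit and the boosters worked at three months, one dropout rule applied to everyone removes more controls than booster participants. The controls who remain then look too active, and the difference shrinks. Longer-term maintenance is the evidence gap that the Background gives as the reason for the trial, so this comparison matters even though it is secondary.

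**Working it through.** **Inputs from the article (Sample size).** Difference: "We assume a mean difference of 400,000 counts per week between the intervention and control groups". SD: "assuming a standard deviation of 1.2 million counts/week". Test: "as statistically significant at the 5% (two-sided) level using a two independent samples t-test". Stated power: "With 450 subjects (300 intervention: 150 control), the trial will have 90% power to detect this mean difference".

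**Assumed, because the article gives no figure.** Further loss q between three and nine months, among those measured at three months; correlation rho between the two readings; how strongly loss depends on three-month activity; and a nine-month difference equal to the three-month target.

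**1. The plan's own figure.** SE = SD × √(1/n_booster + 1/n_control) = 1.2 × √(1/300 + 1/150) = 0.12 million. Power = Φ(0.4/0.12 − 1.96) = Φ(1.373) = 91.5% (91.4% by noncentral t). The stated 90% is reproduced. It refers to three months; no power is claimed for nine.

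**2. Precision at nine months, with loss unrelated to activity.** Start from 450 measured at three months. The t-test uses 300(1−q) and 150(1−q) people. A likelihood model of both readings multiplies the variance of the nine-month difference by 1 − rho²q (large-sample result, nobody returning after a missed three-month visit).

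Example with q = 0.20 and rho = 0.6:
- t-test: SE = 1.2 × √(1/240 + 1/120) = 0.1342; power = Φ(0.4/0.1342 − 1.96) = 84.6%.
- Joint model: factor 1 − 0.36 × 0.20 = 0.928; SE = 0.1342 × √0.928 = 0.1292; power = 87.2%.

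| Further loss q | t-test | Joint, rho 0.4 | Joint, rho 0.6 | Joint, rho 0.8 |
|---|---|---|---|---|
| 5% | 90.1% | 90.4% | 90.6% | 91.0% |
| 10% | 88.5% | 89.0% | 89.6% | 90.5% |
| 20% | 84.6% | 85.8% | 87.2% | 89.1% |
| 30% | 79.6% | 81.5% | 84.0% | 87.3% |

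The power given up is 0.3 to 7.7 points, and at most about 2 points when further loss is 5-10%.

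**3. Loss that depends on three-month activity, same rule in both arms (simulation).** Of 600 randomised, 27.5% are missing at three months, leaving 600 × 0.725 = 435 (290:145). The true effect is 0.4/1.2 = 0.333 SD at both visits.

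- With 15-25% further loss at mean activity, odds of loss 1.6-2.7 times higher per SD lower three-month activity, and rho 0.5-0.7, the t-test averages 0.302-0.328 SD with 74-84% power. The joint model averages 0.332-0.334 SD with 82-88% power.
- The shortfall is (0.333 − 0.328)/0.333 = 2% to (0.333 − 0.302)/0.333 = 9%. In counts that is 0.005 × 1.2 million = 6,000 to 0.031 × 1.2 million = 37,000 per week. The power loss is about 2.5-12 points. It exceeds step 2 at comparable loss because the t-test estimate is also pulled towards zero.
- With 5% further loss, the bias is a few per cent at most and the power loss about 0-3 points.
- With no true effect at either visit, 25% loss and 2.7-fold odds, the t-test averages −0.001 SD and its type I error is 5.1%.

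**4. Loss that differs between arms (large-sample simulation, true difference 0.40 million).**

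| Loss, control / booster | Dependence on activity | rho | t-test | Joint model |
|---|---|---|---|---|
| 15% / 15% | none | 0.6 | 0.40 | 0.40 |
| 15% / 15% | same in both | 0.6 | 0.40 | 0.40 |
| 20% / 10% | same in both | 0.6 | 0.355 | 0.40 |
| 10% / 20% | same in both | 0.6 | 0.448 | 0.40 |
| 20% / 20% | control only | 0.6 | 0.275 | 0.40 |
| 20% / 20% | booster only | 0.6 | 0.524 | 0.40 |
| 25% / 10% | strong, both | 0.8 | 0.28 | 0.40 |

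Errors of about 0.12 million, some 30% of the target and in either direction, need loss that differs between arms in rate or in pattern. In every row the loss depends only on the observed three-month value, which is the condition under which the joint model is unbiased.

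**The case against.** A prespecified t-test at each visit is a valid, standard method, and the comparison is secondary with no power claim. Every input that drives bias is assumed. The Participants section also says that people withdrawn from active participation will, with consent, still be followed for outcomes, which limits loss between visits. All of this stands, and it keeps the point modest.

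The reading of the text can also be challenged. The sentence on nine-month outcomes closes a paragraph on continuous secondary outcomes such as quality of life and walk distance, so its application to accelerometry is the natural reading but is not spelled out. The imputation sentence mentions follow-up data and does not limit what is imputed to three-month values. A reader might infer that the plan has no missing-data analysis for nine months; the wording does not settle that. The sentence directly follows the three-month primary analysis, so three months is its likelier scope. Even on the wider reading it is only a sensitivity analysis, and the main nine-month estimate would still rest on those measured then.

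Finally, a joint model does little about the 25-30% already expected to be missing by three months, unless they return at nine. That also stands.

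**Conclusion.** The point holds as a moderate, inexpensive improvement to a secondary analysis. As written, the main nine-month accelerometry comparison does not use the three-month readings already held. Under 5-25% further loss, odds of loss 1-2.7 times higher per SD lower activity, and a correlation of 0.5-0.7, the t-test estimate is 0-9% too small and the power loss about 1-12 points. Both ranges rest on assumptions, since the article gives neither late loss nor correlation.

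A reader might go further and infer that the nine-month result will be biased, or could be falsely positive. The documents do not support that. There is no bias if loss is unrelated to three-month activity, or if a common rule applies and the arms do not differ at three months. Under a common rule with a real effect, the bias is towards no effect and the false-positive rate stays at its nominal level. Larger errors in either direction need loss that differs between arms, and nothing in the article indicates that it will. The three-month primary analysis and its sample size are untouched.

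**What to change.** Keep the three-month primary t-test exactly as planned. For nine-month accelerometry, take the combined-booster-versus-control contrast from one linear repeated-measures model of the three- and nine-month readings, with arm, visit, arm-by-visit and an unstructured covariance. Include everyone with at least one valid reading, and report the nine-month t-test beside it.

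Use the same approach only for other continuous outcomes measured at both visits, such as walk distance and SF-12 scores. Categorical and count outcomes need their own methods. State also whether the sensitivity imputation covers nine-month gaps.

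The cost is analysis wording and a standard model; no new data, visits or participants are needed. The downside is that the estimate relies on data being missing at random given the observed readings, and people with no reading at either visit are not recovered.

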### Feasibility study

The main risks to trial success identified by those providing scientific review that the feasibility trial will test are:

1. Recruitment targets for the brief intervention will not be met;

2. The brief intervention will not be effective enough to generate sufficient individuals eligible for the trial;

3. Insufficient eligible individuals will consent to participate in the trial

In the first year a feasibility study will be undertaken to assess the feasibility of both trial recruitment plans and the proposed interventions [26,27]. A total of 3000 invitations will be sent to the patients of general practices situated in a "typical" deprived ward. The aim is for at least 150 people to receive the brief intervention and 60 to be randomised to the three trial arms. This will allow outcome measurement in 15-20 individuals in each study arm to estimate a mean and standard deviation for the primary outcome, physical activity counts/per week from a 7-day accelerometry assessment in each group. The success criteria for the feasibility study will be:

1. At least 60 participants recruited to the pilot trial and 45 having 3 month follow-up measurements including accelerometry completed on the basis of an initial mail-shot to 3000 individuals. (We will not use community recruitment at this stage since it may represent a more limited pool for recruitment that we can use to boost participant recruitment from "hard-to-reach" groups as required in the main trial)

2. At least 70% of those randomised to booster interventions actually receiving the interventions per protocol

3. On the basis of the pilot primary outcome (accelerometry) data collected, the sample size for the main trial will be re-calculated. The trial will not proceed if the revised sample size calculation suggests a total sample size greater than 600 will be required. Assuming the protocol and intervention remain unchanged, the participants recruited during the feasibility phase will be included in the full trial population.

## Discussion

### Choice of study population

We know that physical activity levels in the UK are low in South Asian (Pakistani, Bangladeshi and Indian) and Chinese populations with the lowest levels in the Pakistani and Bangladeshi population [28]. Previous trials of face-to-face interventions or telephone interventions have generally been limited to English speaking populations for practical reasons and there is a lack of community-based trials in deprived and in non-White populations [6]. However, meta-analysis suggests effect sizes from motivational interviewing-based interventions are large in ethnic minority populations [29]. We therefore propose to recruit from an ethnically diverse and socio-economically deprived population including Pakistani, Bangladeshi and Chinese communities by making the initial recruitment process as simple as possible i.e. the return of a postage paid reply card with basic information on preferred language and a phone number to allow a research assistant to make contact. The use of bi-lingual study partners as facilitators, where feasible, will facilitate recruitment of ethnic minority populations and allow assessment of effectiveness of the intervention in a multi-ethnic population.

### Choice of study interventions

Behavioural ("lifestyle") interventions have been shown to be potentially more cost-effective than supervised activity ("structured" interventions) and are also more easily generalisable to populations with access to different facilities [30]. There is evidence for the efficacy of telephone support, as a less expensive alternative to face-to-face physical activity consultations, including some evidence from interventions involving no face-to-face assessment or intervention [15].

Meta-analytical and systematic reviews of physical activity and behaviour change suggest that the transtheoretical model (TTM) of behaviour change is the most commonly adopted theoretical framework for promoting physical activity [31-33]. The TTM has demonstrated effectiveness as an approach to increasing exercise adoption and adherence in adults [32,34-36]. It describes how people modify problem behaviours or acquire positive new ones [11,33,37]. The TTM determines behaviour change as a process rather than a single event and offers practical suggestions for how individuals can change behaviour. It consists of the following constructs: stages of change (describes when people change), processes of change (outlines techniques for helping people to change), decisional balance (weighing up the pro's and con's of change) and self-efficacy (increasing one's confidence to change behaviour) [33]. The TTM offers practitioners a common, validated framework for guiding participants through periods of change and proposes strategies for maintaining positive behaviours. We will also adopt a client centred approach to all interventions based upon the style of motivational interviewing.

Motivational interviewing (MI) is a directive, client-centred counselling style for eliciting behaviour change by helping clients to explore and resolve ambivalence [38]. Motivational interviewing has been used in many settings and ethnic groups and has been shown to impact positively on lifestyle and health outcomes including physical activity behaviours in adults [29,39-41]. MI has been applied in a number of formats including technology-based, such as internet and video, telephone and face-to-face consultations [7,8,39,42-44]. An example of a technology-based intervention adopting an MI approach is The Drinker's Check-up [7,8,43]. The Drinker's Check-up offers a comprehensive assessment of the client's drinking and related behaviours. A key element of the programme is providing feedback that matches the user's individual circumstances, motivational readiness and confidence for changing their behaviour.

### Choice of brief intervention (DVD) preceding the study intervention

We have developed a "brief intervention" using motivational interviewing principles but in the form of an interactive DVD and telephone follow up that would be straightforward to adapt for practical application beyond the research context. Our "brief intervention" is consistent with the NICE guidance (and supporting evidence base) on physical activity and behaviour change interventions [6,9], and is based on interventions of known efficacy that are already in use in Sheffield [28]. The intervention and its development will be described more fully in a further paper.

### Choice of outcome measure

Direct measures of physical activity (rather than self-report measures) used at baseline may themselves increase physical activity. The major MRC-funded ProActive trial of physical activity promotion in people with a family history of diabetes has recently been completed and was reported at the European Diabetes Epidemiology Group 2007 meeting [45]. The investigators suggested that the negative result from this major trial may have been due to the intensive baseline measurement resulting in participants in all arms being equally successful in increasing their activity levels, since recent work suggests assessment can trigger a significant increase in activity levels [46]. There is also concern that the detailed baseline assessment usually carried out in a trial setting is a significantly more intensive intervention than is feasible in everyday practice [19]. We have therefore proposed that direct measurement of fitness and physical activity are only performed three months and nine months after randomisation.

Although the study was designed to measure activity counts per week as the objective measure of physical activity, the Actiheart devices that we are using are also capable of measuring energy expenditure, using a combination of heart rate and activity counts recorded by its two sensors. At the first Trial Steering Committee our Independent Chair suggested a change in the primary outcome, from activity counts to energy expenditure, once the feasibility phase was complete. This would capture exercise intensity as well as frequency and duration, making the study results more meaningful to policy makers as well as more comparable to recent related studies.

